#### 4.7 MULTIPLE COMPARISONS AND MULTIPLICITY

Adjustments for multiple comparisons and multiplicity are not necessary given that only one pre-defined hypothesis will be tested involving a single test and a single primary outcome. Several secondary outcomes are specified and analysed at multiple time points. These will be considered as exploratory in nature and so no correction for multiple testing will be carried out. All secondary outcomes will be reported in the analysis report and any resulting publications to avoid bias arising from selective reporting.

#### 4.8 MODEL ASSUMPTIONS

A key assumption of the Cox model is that of proportional hazards - the survival curves for the two strata must have hazard functions that are proportional over time (i.e. constant relative hazard). The assumption of proportional hazards for the primary outcome will be examined using the log-log plot of survival ( $-\ln(-\ln(\text{survival}))$ ) versus  $\ln(\text{time})$ , examination of the Schoenfeld residuals and formally with a proportional hazards test. If the proportional hazards assumption is violated a suitable alternative survival method will be considered, for example time varying covariates may be included in the analysis model.

Similarly, alternative methods will be considered if any violation of assumptions is detected in any of the methods for the secondary outcomes. In particular linear mixed effects models assume normality of the residuals. The distribution of continuous secondary outcomes will be explored graphically, e.g. using a normal qq-plots. If the outcome is considered to be non-normally distributed a data transform will be considered, e.g. a logarithmic transform for positively skewed data, and analysis will instead be carried out on the transformed data. Otherwise bootstrapping may be used to generate standard errors and confidence intervals that are valid under departures from normality in the dataset.

## 5 SECONDARY ANALYSIS

### 5.1 PRIMARY OUTCOME

Secondary analysis will consider the individual components of the primary composite outcome in the ITT population, i.e. cardiovascular disease and onset of or hospitalisation, separately, and also all-cause mortality. Time to event will be defined as time from randomisation (RANDDAT) to time of each of the following: time of first onset of or hospitalisation (HOSPDAT), time of first onset of cardiovascular disease (CVDSTDAT), or time of death (DEATHDAT). Additionally time to death from cardiovascular disease will be analysed separately. Death from cardiovascular disease will be coded from the derived from DEATHTYPE (death from cardiovascular disease DEATHTYPE=1).

If a participant experiences more than one endpoint then time to event will be computed from the time of the first occurrence of the relevant event i.e. time to each component will be computed the time to that event even if another component of the primary endpoint occurs earlier). Where relevant competing risks (e.g. mortality, where a participant dies before the end of the study without experiencing another relevant endpoint) will be treated as a form of non-informative censoring, with censoring taken as the time point at which the competing risk occurred. Censoring for those participants who complete the study or withdraw from follow-up will be treated in the same way as for the primary outcome, i.e. censoring will occur at the date of last follow-up for all participants on an ITT basis.

The cox proportional hazards approach will be repeated for individual components of the primary composite endpoint and all-cause mortality as secondary analyses, adjusting for GP practice. Time to event will be summarised using median and range for each endpoint and model estimates will be presented as hazard ratios with associated p-values (see table 7).

TABLE 3 DUMMY TABLE FOR COMPONENTS OF THE PRIMARY OUTCOME

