|           | 1. The individual components of the composite primary outcome                                  | 
 
Hospitalisation or new onset heart disease (coronary heart disease, arrhythmia, atrial fibrillation, suddendeath, resuscitated sudden death), stroke, transient ischaemic attack, peripheral arterial disease or heart failure.
 
 | 
 
Total occurrences
 
                                                      |
|           | 2. Measures of cardiovascular haemodynamics                                                    | 
 
Change in blood pressure annually and at final visit.
 
                                                                                                                                                                           | 
 
Annually and at final visit.
 
                                           |
|           | 3. Measures of renal function                                                                  | 
 
Changes in NP
 
Change in ACR
 
Changes in eGFR
 
                                                                                                                                                                   | 
 
Change from baseline, annually and to final visit for NP, ACR and eGFR
 
 |
|           | 4. Healthcare cost evaluation                                                                  | 
 
Change in health status on EQ-5D-5L, KDQoL, (ICECAP-A and QoL VAS – Oxford only) and NHS resource use (records).
 
                                                                                                                | 
 
Change from baseline, annually and to final visit
 
                      |

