## 12.2. Description of Statistical Methods

In accordance with CONSORT guidelines, we will record and report participant flow. Descriptive statistics of recruitment, drop-out, and completeness of interventions will be provided. Baseline variables will be presented by randomised group using frequencies (with percentages) for binary and categorical variables and means (and standard deviations) or medians (with lower and upper quartiles) for continuous variables. There will be no tests of statistical significance nor confidence intervals for differences between groups on any baseline variables.

The primary analysis will be on an intention-to-treat basis. That is, after randomisation, participants will be analysed according to their allocated treatment group irrespective of what treatment they actually receive. The primary outcome will be analysed using a survival analysis method, such as Cox proportional-hazards model, adjusting for practices. Results will be presented as hazard ratios with 95% confidence intervals and associated two-sided P-values. To test the robustness of the result, a sensitivity analysis will be carried out, using the same method, adjusting the following pre-specified baseline prognostic factors: diastolic and/or systolic blood pressure above or below NICE target, type II diabetes and coronary artery disease.

Same approach will be repeated for individual components of the primary composite endpoint and all-cause mortality as secondary analyses. Analyses for other outcomes will be carried out using multiple log-binomial regression models for binary data and linear mixed effect model for continuous data collected over time.

Assumption of proportional hazards will be examined and if any of the assumptions were violated, a suitable alternative survival method will be considered. Similarly, alternative methods will be considered if any violation of assumptions is detected in any of the aforementioned methods for other outcomes.

Adverse effects will be tabulated according to randomised group assignments and the proportions will be compared using Fisher's exact test.

A full detailed analysis plan, including approach of handling missing data, subgroup analyses, and sensitivity analyses, and a plan for interim analysis will be prepared before the final datalock and analysis by a statistician who is independent from the study. All analyses will be performed by the trial statistician and validated by a separate statistician.

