### 2.2.2 PRIMARY LONG-TERM OUTCOMES

Annual rates collected via medical notes review of death, hospitalisation for heart disease (coronary heart disease, arrhythmia, atrial fibrillation, sudden death, resuscitated sudden death), stroke, transient ischaemic attack, peripheral arterial disease or heart failure. First onset of any condition listed above not present at baseline.

The following variables will be used to record the occurrence of an event HOSPYN (hospitalised), FSONSETCVD (first onset of cardiovascular disease) and DEATHYN (death). In addition the endpoint will be adjudicated by the endpoint committee (DECISION). If the event is not judged to be an endpoint according to the protocol OR it is not the first onset of hospitalisation for CVD, or death OR there is insufficient information to determine it is an endpoint according to the protocol OR the endpoint committee determines it does not constitute as an endpoint for any other reason then the external adjudication will be coded "No". The reason that the event does not meet the endpoint condition will be captured in the variables REASONIFNO and OTHREASONIFNO. If any of the previously mentioned variables are coded "Yes" and DECISION is coded "Yes" then a primary outcome event will be recorded as having occurred.

If more than one primary outcome event has occurred, time to event will be computed using the date of the earliest occurring event minus RANDDAT (date of randomisation).

If a participant does not experience a primary outcome event they will be censored either at the date of last follow-up, the date of last contact or at the date of withdrawal from the study. Based on the intention to treat (ITT) principle, participants who withdraw from treatment but consent to further follow-up will be censored at the date of last contact rather than the date of withdrawal from treatment.

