**Summaries of data:**

|                                                                    | TREATMENT
(N%) |                   | CONTROL
(N%) |                   | OVERALL           |
|--------------------------------------------------------------------|-------------------|-------------------|-----------------|-------------------|-------------------|
|                                                                    | AVAILAB
LE N   | SUMMA
RY       | AVAILAB
LE N | SUMMA
RY       | SUMMA
RY       |
| Time from randomisation to cardiovascular disease                  | N                 | Median
(Range) | N               | Median
(Range) | Median
(Range) |
| Treatment effect  , [95% Confidence interval], p-value |                   |                   |                 |                   |                   |
| Time from randomisation to hospitalisation                         |                   |                   |                 |                   |                   |
| Treatment effect  , [95% Confidence interval], p-value |                   |                   |                 |                   |                   |
| Time from randomisation to all-cause mortality                     |                   |                   |                 |                   |                   |
| Treatment effect  , [95% Confidence interval], p-value |                   |                   |                 |                   |                   |
| Time from randomisation to mortality from cardiovascular disease   |                   |                   |                 |                   |                   |
| Treatment effect  , [95% Confidence interval], p-value |                   |                   |                 |                   |                   |

1. Hazard ratio as estimated from the cox-proportional hazards model, adjusted for GP practice.

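### SAP 5.1 and Table 3 omit the disease-level components and total occurrences listed as secondary outcome 1, and do not say whether component events must be adjudicated

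*Combined protocol and SAP*

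**What the plan says.** - **Protocol section 6** gives the first secondary objective as "The individual components of the composite primary outcome". The outcome measure opens with "Hospitalisation or new onset heart disease (coronary heart disease, arrhythmia, atrial fibrillation" and goes on to stroke, TIA, PAD and heart failure. The time-point column reads total occurrences. SAP 1.4 carries the same entry, twice.
- **Protocol 12.2** gives the method: "Same approach will be repeated for individual components of the primary composite endpoint and all-cause mortality as secondary analyses". The approach meant is the survival model used for the primary outcome.
- **SAP 5.1** says what it takes components to be: "individual components of the primary composite outcome in the ITT population, i.e. cardiovascular disease and onset of or hospitalisation, separately, and also all-cause mortality". Cardiovascular death is added later in the paragraph. On ordering it says "time to each component will be computed the time to that event even if another component of the primary endpoint occurs earlier".
- **SAP Table 3** has four rows: cardiovascular disease, hospitalisation ("Time from randomisation to hospitalisation"), all-cause mortality and cardiovascular mortality.
- **SAP 2.2.2** lists alternative grounds on which DECISION is coded No. One is that "it is not the first onset of hospitalisation for CVD, or death". The reason for a No is kept in REASONIFNO and OTHREASONIFNO.
- **SAP section 11** names only the handling of PAD as a difference from the protocol.

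**The concern.** The outcome the trial lists and the analysis the SAP specifies are different quantities. Protocol section 5 and SAP 1.3 both single out heart failure and sudden cardiac death as the distinctive cardiovascular risk in CKD, yet neither has a planned estimate. A reader of the trial report would expect disease-level results and would have no pre-specified analysis to check them against.

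The adjudication gap matters because the trial is open-label and, under SAP 2.5, its statisticians are not blinded. Blinded adjudication is stated for the primary endpoints only. If component definitions, event dates and the adjudication requirement stay open, they may be settled by people who know the allocation. SAP 4.7 undertakes to report every secondary outcome so as to avoid selective reporting. That undertaking cannot be checked for an outcome whose analysis is not defined.

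**Working it through.** No sample size, power or alpha figure bears on this point, so there is no plan figure to reproduce. The check is a comparison of texts, followed by a small illustration.

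**Step 1: listed components against planned rows.**

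| Listed in protocol 6 and SAP 1.4 | Row in SAP Table 3 | Variable named in the SAP for the event |
|---|---|---|
| Heart disease, with subtypes | none | HDYN; none by subtype |
| Stroke | none | STROKEYN |
| TIA | none | none |
| PAD | none | PADYN |
| Heart failure | none | HFYN |

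Five disease groups are listed, and none matches any of the four planned rows. The four variables appear in SAP 4.1.1 only to date the composite. HFYN is also the name of the baseline heart failure history item in SAP 3.2. SAP 2.2.3 has no subsection for components. SAP Appendix III lists TIA as a secondary outcome, but no analysis follows.

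**Step 2: total occurrences.** Protocol 12.2 and SAP 5.1 offer only time-to-event models. No count or summary of total occurrences is specified for the components.

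**Step 3: the adjudication rule.** The ground quoted from SAP 2.2.2 is garbled and can be read in two ways.
- Reading A: an event is coded No if it is not the participant's first.
- Reading B: an event is coded No if it is not a qualifying type (first onset of CVD, hospitalisation for CVD, or death).

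SAP 5.1 does not say whether a component event needs DECISION = Yes. Under A, requiring Yes cuts off every component at the participant's first event, and not requiring it lets in events that were not accepted. Under B, later qualifying events keep a Yes and nothing is lost.

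**Step 4: illustration of Reading A with DECISION = Yes required.** The documents give no rates by disease, so the disease-level loss cannot be calculated. SAP 2.4 does give a CV event rate a = 0.1129 and a death rate b = 0.0476 per person-year. With independent exponential times (assumed) over 3 years, the share of deaths preceded by a CV event is

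1 − [b/(a+b) × (1 − exp(−3(a+b)))] / [1 − exp(−3b)]

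- SAP rates: b/(a+b) = 0.0476/0.1605 = 0.2966; 1 − exp(−0.4815) = 0.3821; product 0.1133; 1 − exp(−0.1428) = 0.1331. Share = 1 − 0.1133/0.1331 = about 15%.
- Both rates × 0.667 (the SAP's multiplier for eGFR 45-50): 1 − 0.0815/0.0909 = about 10%.
- Both rates × 0.5: 1 − 0.0635/0.0689 = about 8%.

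Positive correlation between CV events and death would raise these shares; lower event rates would reduce them.

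**The case against.** The composite is itself set out in three parts: death, hospitalisation and first onset. SAP 5.1 splits along those lines, so its rows are genuine endpoint types. SAP 1.4 keeps the disease list, variables for most of the diseases exist, and a later sentence in 5.1 says the Cox approach is repeated for the individual components. SAP 4.7 calls the secondary outcomes exploratory and promises to report them all. On this view the plan is merely short on detail.

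Part of this stands. The data probably exist, and the outcome could be analysed. But the later sentence in 5.1 names no components, while the explicit definition earlier in the section and the four rows of Table 3 do. A statistician following them would produce a different analysis from the listed outcome. Calling an outcome exploratory removes the multiplicity correction, not the need to define it.

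A reader might infer something stronger: that every event after a participant's first is coded No and lost to the component analyses. The documents do not support that. SAP 2.2.2 and 4.1.1 both provide for several primary outcome events in one participant and take the earliest, which would be unnecessary if later ones were always rejected. The DECISION rule is written to derive the primary outcome and is not said to govern components. SAP 5.1 expressly times a component past an earlier one. Rejected events also stay in the data with a reason.

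A reader might also infer that pooled hospitalisation hides effects running in opposite directions across diseases. Nothing in the documents bears on that.

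**Conclusion.** The mismatch is established from the text. Secondary outcome 1 is listed by disease and as total occurrences; none of its five disease groups and no total-occurrence summary is analysed, and the departure is not declared.

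The adjudication point is an unresolved conflict between SAP 2.2.2 and 5.1, not a demonstrated loss. Later component events could be excluded or used unadjudicated if the first-event reading is applied. The effect ranges from zero under the qualifying-type reading to, for deaths only and assuming independence, roughly 8% to 15% of 3-year deaths under the strict reading with DECISION required. That range illustrates scale only. It does not carry over to stroke, heart failure or any other single disease.

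This should be corrected, but it does not threaten the trial's main conclusion: the primary analysis uses only the earliest event.

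**What to change.** 1. Add Table 3 rows for coronary heart disease, arrhythmia or AF, sudden and resuscitated sudden death, stroke, TIA, PAD and heart failure. Keep the two mortality rows. For each row name the variable, the event date and the model, and give the heart failure endpoint a name distinct from the baseline item.
2. Analyse each row as time to the first adjudicated event of that type, and report total occurrences per arm beside it. This serves both the Cox method in protocol 12.2 and the counts in the outcome tables.
3. State in SAP 5.1 that a component event must be accepted by the committee against the endpoint definition irrespective of order. Reword the ground in SAP 2.2.2 to match, and record first-event status as a separate flag.
4. Use REASONIFNO and OTHREASONIFNO to find any event coded No only because of its order. Send these for blinded review if they were never assessed against the definition.
5. Enter the change in SAP section 11.

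The cost is SAP wording, a few more exploratory models, some of them on small counts, and possibly a limited re-review. It assumes the endpoint form separates the disease types. SAP 4.1.1 supports this for four groups; for TIA and the heart disease subtypes it needs to be confirmed.

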**Summaries of data:**

|                                                                    | TREATMENT
(N%) |                   | CONTROL
(N%) |                   | OVERALL           |
|--------------------------------------------------------------------|-------------------|-------------------|-----------------|-------------------|-------------------|
|                                                                    | AVAILAB
LE N   | SUMMA
RY       | AVAILAB
LE N | SUMMA
RY       | SUMMA
RY       |
| Time from randomisation to cardiovascular disease                  | N                 | Median
(Range) | N               | Median
(Range) | Median
(Range) |
| Treatment effect  , [95% Confidence interval], p-value |                   |                   |                 |                   |                   |
| Time from randomisation to hospitalisation                         |                   |                   |                 |                   |                   |
| Treatment effect  , [95% Confidence interval], p-value |                   |                   |                 |                   |                   |
| Time from randomisation to all-cause mortality                     |                   |                   |                 |                   |                   |
| Treatment effect  , [95% Confidence interval], p-value |                   |                   |                 |                   |                   |
| Time from randomisation to mortality from cardiovascular disease   |                   |                   |                 |                   |                   |
| Treatment effect  , [95% Confidence interval], p-value |                   |                   |                 |                   |                   |

1. Hazard ratio as estimated from the cox-proportional hazards model, adjusted for GP practice.

## 6 SENSITIVITY ANALYSIS

### 6.1 COVARIATE ADJUSTMENT

To test the robustness of the result for the primary outcome, a sensitivity analysis will be carried out, using the cox proportional hazards model, adjusting the following pre-specified baseline prognostic factors: diastolic (DIABPR/DIABPL) and/or systolic blood pressure (SYSBPR/SYSBPL) above or below NICE target, type II diabetes (DIAYN) and coronary artery disease (IHDYN) BP targets will be based on the following measures of clinical blood pressure:

- People aged under 80 years: lower than 140/90 mm Hg (systolic/diastolic)
- People aged 80 years or over: lower than 150/90 mm Hg (systolic/diastolic)

As blood pressure is recorded in both arms at each visit, we will consider the average of the two measures as meeting the criteria.

**TABLE 4 DUMMY TABLE FOR THE ANALYSIS OF THE PRIMARY OUTCOME**

| HAZARD RATIO  | 95% LOWER C.I. | 95% UPPER C.I. | P-VALUE |
|---------------------------|----------------|----------------|---------|
|                           |                |                |         |

1. Adjusted for the following covariates: systolic or diastolic blood pressure above NICE target, type II diabetes, coronary artery disease and GP practice.

